### Primary outcome

The primary outcome of the study is the proportion of patients in each group who complete the FOBT test and returned it within four months. The proportion of patients in the intervention group who access the telephone support line and/or website will be determined. Of those who access the patient aids, the number of patients who complete their FOBT will be determined to facilitate evaluation of whether access to the patient aids by intervention group patients increased their rate of FOBT completion compared to the control group patients. Our findings will assist in determining whether the patient aids offered to the intervention group may be a useful tool to support FP in their CRC screening efforts and improve patient uptake of the test.

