Research has shown a majority of patients completing the FOBT do so within 4 to 6 weeks [20]. In order to allow adequate time to complete the FOBT and return it to the laboratory, patients will be given four months to do so. Those patients not returning their FOBT test within a period of four months will be scored as failing to complete the FOBT test.

Analysis of results will be based on the intention to treat (ITT) model. All Statistical analysis will be performed using SAS 9.2 ® software. Categorical variables will be compared using the Chi-square test. The time taken to return FOBT cards will be analyzed with Cox’ Proportional Hazards Regression analysis. Due to the clustered design, study outcomes will be measured at the level of the patient, family physician, and medical clinic/cluster. The analysis will utilize multi-level logistic regression that accounts for variance among patients with the same FP, FP within the same cluster, and among the clusters. The SAS® GLIMMIX procedure will be used to model patient FOBT completion rate (response variable). This will enable evaluation of the rate of patient FOBT compliance within medical clusters and individual FPs. Sources of variance included in the model will include cluster level (treatment, electronic medical record or paper charts, PIN and/or UPCON membership), family physician level (gender, solo/group practice), and patient level (age, gender, socioeconomic status, and previous FOBT screening history) variables as well as random variation.

A computerized randomization number list will be used to select 10 patients per FP to be contacted for a Post-Study Follow-Up Survey (Additional files 4 and 5) conducted by telephone. Only those patients providing permission to be contacted will be included. Those patients surveyed will be asked for permission to document their Personal Health Identification Number which will facilitate future studies conditional to Health Research Ethics Board (HREB) approval of analysis of repeat colorectal cancer screening behavior over time.

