### Experimental treatment group

All FPs will follow their usual clinical practice for CRC screening with the FOBT during the patient periodic health examination. FPs in the intervention group will provide patients with access to the study specific colorectal cancer information and screening nurse-managed telephone support line and website by giving them a refrigerator magnet with the telephone number and website URL (Figure 2). Access to the telephone support line and/or website is patient initiated. All patients in both treatment groups will be assigned a study-specific, seven character, alpha-numeric identification number. For patients allocated to the intervention group, each patient’s magnet will be assigned the same study-specific identification number which will be used by patients in the experimental group to access the telephone and website patient aids, facilitate tracking patient use of the intervention support tools, and protect personal health information.

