### The colorectal cancer information and screening telephone support line and website

The scientific literature and credible health resources [1,3,8,9,11-13] will be used to gather patient relevant colorectal cancer and screening information. Patient health education files will be generated based on this information to address patient’s most common questions and issues related to FOBT screening [3,8-10]. A survey conducted in Manitoba [3] and personal communications between the study coordinator (KC), family physicians and their support staff, and lab technicians will also inform the development of the patient decision aids. Website resource development was based on the same information in addition to feedback from CRC patients/survivors (n = 4), two small groups (n = 5–8) of average risk men and women, and the PCO-NET group during three quarterly workshops.

Each patient will provide the registered nurse taking the call with their personal seven digit alphanumeric study identification number. Similarly, patients logging on to the website will be guided to enter their study identification number and create a personal password that allows them access to the site. Patients initiating a call to the telephone line will be able to ask questions which will be answered by a registered nurse using the health education files. If a patient asks a question to which there is no health education file/answer, the question will be documented by the registered nurse and the patient given the contact information of the study coordinator and/or provided the website address. Patients logging on to the website are able to view each webpage according to their specific questions and areas of interest (Figure 3 for website site map). Each page visited by each patient will be recorded. Patients will be able to email the study coordinator if they have further questions/comments. We will be able to track the number of calls made by each patient, the health education files accessed by each patient, the number of times they access the website and the website content/pages they visit, as well as any additional questions asked that were not contained in the health education files or website. Patient study identification number will correspond to the study identification number on the Patient Tracking Form which facilitates linking patient demographic information, FOBT completion status, and In-Clinic and Follow-Up Survey data with telephone and website usage.

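### The comparison of aid users with controls sets no time order between access and FOBT return, so it is biased if the chance of access changes at return

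*Protocol article*

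**What the plan says.** The primary outcome in the protocol article is a comparison of randomised groups: "the proportion of patients in each group who complete the FOBT test and returned it within four months". The statistical section adds "Analysis of results will be based on the intention to treat (ITT) model".

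The same Primary outcome section then plans a second comparison. "Of those who access the patient aids, the number of patients who complete their FOBT will be determined", so that it can be judged whether access "increased their rate of FOBT completion compared to the control group patients". The subset (intervention patients who used the aids), the comparator (control patients) and the causal purpose are all stated. No order between access and return is stated, and no window in which access counts.

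Other sections bear on this:

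- Experimental treatment group: "Access to the telephone support line and/or website is patient initiated".
- Telephone support line and website: "We will be able to track the number of calls made by each patient". The list goes on to education files, website visits and pages. It names counts and content, but no dates of access.
- Description of the study protocol: the physician records the date of FOBT completion.
- Statistical analysis: patients have four months, and "a majority of patients completing the FOBT do so within 4 to 6 weeks". "The time taken to return FOBT cards will be analyzed with Cox" regression; access is not named as a covariate.
- Sample size: the power statement splits patients 80%/20% into those who do not and do use the magnet.
- Discussion: possible policy change is tied to whether utilisation raises compliance.

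**The concern.** Access happens after randomisation and competes in time with the outcome. A patient who returns the test in week 2 has had two weeks in which to need the aids for doing it. A patient who never returns it has four months. If people stop consulting the aids once the test is in, early completers are under-represented among users, and users look worse than they should. In the other direction, a patient may return the test and only then look at the website. Counted as a user who completed, that patient makes the aid look effective although access could not have caused completion.

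What is at stake is the statement that using the aids raises completion. The Discussion leans on that statement for its policy conclusion.

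**Working it through.** The plan gives no figure for this analysis, so there is none to reproduce. The check asks what the user proportion shows when the aid does nothing.

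**Formula.** Let c be true completion, q1 the chance that a completer is counted as a user, and q0 the same chance for a non-completer. Completion among users = c·q1 / [c·q1 + (1 − c)·q0]. It equals c when q1 = q0. Any bias therefore comes from q1 differing from q0.

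**Inputs from the protocol.** c = 0.40 (power statement) or 0.42 (current rate in the text); four months, taken as 17.3 weeks or 120 days; 20% users.

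**Assumed inputs.** Inert aid; access unrelated to inclination. Return times of completers are gamma with shape 2.5 and scale 2.3 weeks (median 5.0 weeks, in line with the 4 to 6 weeks quoted). The access patterns are those below; none comes from the documents.

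**1. Access independent of return, counted at any time.** q1 = q0, so users show 40%. The bias is zero, even though some completing users looked only after return.

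**2. Access stops at return.** For exponential access times with mean m weeks, q1 = 1 − (1 + 2.3/m)^(−2.5) and q0 = 1 − exp(−17.3/m). In the constant-rate row, 1/m is replaced by 0.0181 per week, which gives 20% ever use.

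| Access pattern | q1 | q0 | Completion among users | Bias (points) |
|---|---|---|---|---|
| Mean 1 week | 0.949 | 1.000 | 39% | -1 |
| Mean 2 weeks | 0.852 | 1.000 | 36% | -4 |
| Mean 4 weeks | 0.679 | 0.987 | 31% | -9 |
| Constant rate over four months | 0.097 | 0.269 | 19% | -21 |

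Example, mean 4 weeks: 0.40 × 0.679 / (0.40 × 0.679 + 0.60 × 0.987) = 0.2716 / 0.8638 = 0.314. In the first three rows only the ratio q1/q0 matters, so the 20% use rate cancels. A simulation of 2,000,000 patients gave 0.388, 0.362, 0.314 and 0.193 for the four rows.

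**3. Access only halved after return.** Take c = 0.42, gamma return times with shape 3 and scale 13.1 days (median 35 days), and q1 midway between its value in step 2 and q0.

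- Mean access time 7 days: the pre-return chance is 0.958 and q0 = 1.000, so q1 = 0.979. Users show 41.5% (-0.5 points).
- Mean access time 60 days: the pre-return chance is 0.447 and q0 = 0.865, so q1 = 0.656. Users show 35% (-7 points).

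**4. Completion prompts a later look.** Take c = 0.42. In every group 20% access the aids independently of return, and an extra share e of completers look after return. Then q0 = 0.20 and q1 = 1 − 0.80 × (1 − e).

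- e = 5%: q1 = 0.24; 0.1008 / (0.1008 + 0.1160) = 46.5% (+4.5 points).
- e = 10%: q1 = 0.28; 0.1176 / (0.1176 + 0.1160) = 50% (+8 points).

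The two mechanisms can also act together. With c = 0.40, access stopping at return with mean 2 weeks, and 20% use overall, q1 = 0.181 and q0 = 0.213. If 10% of completers also look after return, q1 = 1 − 0.819 × 0.90 = 0.263 and users show 45% (+5 points).

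**5. Counting only access before return, in a simple proportion.** This uses the same q1 as step 2, so it creates a bias even where step 1 had none. With independent access it gives 39%, 36% and 31% for means of 1, 2 and 4 weeks. For access spread evenly over four months, q1/q0 is mean return time over window = 5.75/17.3 = 0.332, and users show 0.40 × 0.332 / (0.40 × 0.332 + 0.60) = 18%.

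**6. Access as a time-dependent covariate.** 20,000 simulated patients, inert aid, 42% completion, 20% potential users, mean access time 30 days:

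| Access after return | Odds ratio, ever-users against control rate | Time-dependent Cox hazard ratio (SE of log) |
|---|---|---|
| Unchanged | 1.03 | 1.04 (0.03) |
| Halved | 0.87 | 1.04 (0.03) |
| None | 0.71 | 1.04 (0.03) |
| Extra 10% of completers | 1.43 | 1.04 (0.03) |

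The hazard ratio is the same in each row by construction, because only access before return enters the model. It is compatible with 1.

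**The case against.** **The rule is read from silence.** A reader might infer that patients are to be classed as users if they ever accessed the aids, whatever the order. The article does not say that, and a condensed article may leave the definition of a user and its window to the full protocol or analysis plan. This stands, and the missing definition is not the point made here. What the article does fix is the subset, the comparator and the causal purpose, and a crude proportion among users misleads under either natural definition (steps 2, 4 and 5).

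**Timing alone is not enough.** It is tempting to say that the error would arise even if users were a random sample. Step 1 shows that it would not. A behavioural change at return is needed. Such a change is plausible, since the aids explain a test that the patient has by then finished, but the documents give no data on it.

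**The main result is safe.** Because the text sits under Primary outcome, a reader might infer that the primary comparison is compromised. It is not. That comparison is by randomised group under intention to treat, and access is not among the listed terms of the multilevel model.

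**Self-selection is the larger problem.** Users choose themselves and are set against all controls. Correct time order does not cure this. A patient who has already decided to do the test may log on for instructions, and even the time-dependent model would credit the aid. This stands in full and limits what the fix can claim.

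**The extreme figure is extreme.** The -21 points needs a constant access rate for four months and complete cessation at return. If access clusters in the first week, the bias is about -1 point.

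**Conclusion.** The point holds in a limited form. The stated comparison of users with controls has no time order between access and return, and it is used to judge whether access raised completion. If the chance of access changes at return, an inert aid can appear harmful by about 1 to 21 points (access stops at return), or helpful by about 4.5 to 8 points (an extra 5% to 10% of completers look only afterwards). If access is independent of return, the timing bias is zero. The direction cannot be known beforehand, and at the upper end the artefact is as large as the 15-point effect the trial seeks.

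These sizes rest on assumed access patterns and an assumed shape of return times. Only the completion rate, the four-month window, the 4-to-6-week return and the 20% use come from the protocol. The exposure is confined to the user analysis and to conclusions phrased in terms of utilisation.

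**What to change.** - Do not use the crude completion proportion among users as evidence of effect, whether it counts any access or only access before return. It may be reported as a description of use.
- Record the date of every call and log-in. The listed tracking items do not mention dates, so it should be confirmed that the logs keep them.
- In the Cox model already planned for time to return, with time counted from the visit, enter access as a time-dependent covariate: 0 until first access, 1 afterwards.
- Label this analysis exploratory, because patient-initiated use remains confounded by motivation.
- Base the efficacy and policy conclusions on the randomised intention-to-treat comparison, and reword the Discussion accordingly.

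Cost: access dates must be kept in the telephone and website logs, and the analysis takes a little more work. The FOBT completion date is already collected. If dates were not kept, the time-dependent analysis cannot be done, and user completion should then be reported as description only.

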### Secondary outcomes

Secondary outcomes of the study include determining the most common questions of average-risk Manitoban patients’ related to CRC and FOBT screening and evaluating their experience with the telephone support line and/or website including helpfulness, number of times accessed, and preference for the telephone support line and/or website. Factors related to patient noncompliance will also be evaluated in post-study Follow-Up Survey. Each FP collaborating on the study was asked to complete a Family Physician Survey developed specifically for the study and will provide feedback from family physicians related to FOBT screening, their experience participating in this practice-based primary care research study, and the implementation/utilization of the patient aids in their clinical practice. All FPs will be provided with the study findings. In particular, FPs will be provided with their patient FOBT completion rates as well as those of their colleagues and the clinics collaborating in the study. All findings are confidential and reported anonymously. Costs of implementation of both the telephone support line and website will be evaluated.

## Discussion

Family physicians understand that colorectal cancer screening using the FOBT is effective in reducing colorectal cancer mortality and their patients are becoming more aware of the importance of screening. However, along the trajectory of colorectal cancer screening, a complex set of barriers exists for both family physicians and their patients.

If our findings demonstrate that utilization of the telephone support line and/or website result in clinically significant increases in FOBT compliance by average-risk Manitobans, changes in CRC screening at the policy- and system-level may be warranted. A strong and trusting family physician-patient relationship, combined with the patient intervention (education and decision aid) and public health programs to increase awareness of CRC and screening (ColonCheck Manitoba) has the potential to increase FOBT CRC screening rates, decrease CRC mortality and morbidity and improve the health of Manitobans.

It is expected that the patient-centered strategies outlined in the above protocol will support family physicians in improving patient understanding of CRC, the importance of FOBT screening in average-risk individuals as well as providing specific instructions on how to conduct the FOBT. Hence, it has the potential to lead to improved rates of patient FOBT compliance. Clinic, physician, and patient level variables associated with FOBT completion will be assessed for potential usefulness in planning strategies to target specific high-risk patient populations that require additional focus and supportive strategies for family physicians in Manitoba.

It is unknown what level of comfort/ease/acceptance Manitoban patients in the appropriate age range for CRC screening have with accessing/utilizing web-based health information and whether it has potential to be an effective venue through which FP could provide preventive health information to patients. This study will attempt to shed some light in this area.

Even if the outcome of the outlined study is negative, the findings will provide useful information regarding the limitations of the guaic based FOBT test in CRC screening and barriers to patient completion of the test. New potential research directions and study questions may also be generated.

Family physicians interested in collaborating in research face challenges including time pressures, minimal infrastructure to support the additional requirements of research, and lack of access to information about on-going research projects. In addition, their role primary healthcare research is often undervalued. We will document the factors involved in establishing the collaborative partnerships with the community-based family physicians in the outlined protocol.

This will allow us to contribute to the limited existing knowledge regarding successful partnerships among primary healthcare researchers and community-based family physicians as well as the unique requirements to support integrated knowledge translation and evidence-based decision making.

### Limitations

There are a few limitations of this study protocol which are outlined as follows:

(1) Inclusion of the In-Clinic Patient Survey in both treatment groups may raise patient awareness about CRC and screening sufficiently to affect/improve screening rates even without the intervention (magnet). To address this we will look at the CRC screening rates in the control group and compare them to historical rates.

(2) Those family physicians agreeing to participate in the study may have done so with awareness that their patients (screening process) have a relatively higher screening rate and degree of success with screening. FP declining to participate may have lower patient CRC screening rates and be concerned about participating, the perception of being evaluated, and how it reflects on their practice. It may be that these FP-patient populations have the most to gain/highest potential to benefit from the intervention. It may be that, in certain populations, the intervention increases screening rates more than in others.

(3) Some providers (PIN and UPCON) are involved in other quality improvement interventions. Therefore, these clinics may have a specific approach to screening that has already lead to improvements in patient CRC screening rates and functioning/practice may be more evidence-based compared to those that are not involved in these initiatives. In these groups, the study intervention may have minimal effect.

(4) Only fee-for service FPs are included. Therefore, the results may be applicable only to this type of provider.

(5) FP and patients represent an urban geographical area and therefore, results may not be generalizable to patient populations in rural areas.

(6) Disparity in accessing the website patient aid is a likely factor for individuals living in rural communities and those with a lower socioeconomic status. Those patients agreeing to the follow-up survey may be more apt to complete the FOBT. Therefore, feedback from those prone to fail to complete the test may be under represented.

### Benefits

There are a number of benefits of the study protocol which are outlined as follows:

(1) The pragmatic design and flexibility of the protocol for each medical practice ensured it reflected the “real world” clinical practice environment and its inherent variability. This approach will produce findings that are generalizable and relevant to community-based family practice and will increase translation and application of evidence-based findings into the clinical practice setting. The study was powered to detect an absolute increase in CRC screening rates of 15% by the intervention. This is a realistic and clinically significant improvement.

(2) The multi-disciplinary team working together on this project represent multiple stakeholder opinions and contributions (primary care providers, primary care researchers, policy makers, and patients). It also reflects a variety of providers/practitioners all of which enhance the pragmatic nature of the design and findings. Working collaboratively on this research project facilitated creation of new networking opportunities and partnerships that have the potential to support future primary healthcare research that inform evidence-based family practice.

(3) Findings will allow us to describe the degree of variability in screening rates among the medical clinics and practitioners involved in the study and, the rates of internet usage among the age category 50–74 for a health-related issue, and more specifically, CRC information and screening.

(4) Findings will provide valuable patient feedback about the FOBT and the common issues related to completion/non-compliance with the test.

(5) The study is highly representative of the community-based clinical practice environment and included a variety of FPs from a number of different areas in the city and practice settings.

